**Figure 3 F3:**
[figure not shown]
Study design and recruitment process. AI, artificial intelligence; BC, breast cancer; DBT, digital breast tomosynthesis; DM, digital mammography.

Women attending the centres for their scheduled mammogram appointment (or those who have had a mammogram within the past month) will receive information about the study and will be invited to participate on a voluntary base. Women who agree to participate, meet the inclusion and exclusion criteria and sign their informed consent document will undergo the MammoWave examination. All the eligible women will be enrolled consecutively. The reason for non-participating in the study (fear of the new exam, lack of time, lack of information, lost-to-follow-up, breasts size larger than MammoWave’s cup) will be recorded by the investigators.

On completion of MammoWave’s scan of each breast, the data will undergo processing in a cloud platform to enable real-time and high-speed data processing. The output from MammoWave will primarily consist of microwave images (along with parameters that characterise these images) and will include the label generated by the novel AI-based classification algorithm; the label will be then used for final analysis by comparing it with conventional imaging results. Thus, the microwave images (which lack detailed morphological definition) and their associated features will not serve as a basis for diagnostic decisions made by radiologists or investigators.

Regarding intervention, if MammoWave’s results (ie, labels provided by its AI classification system) indicate WSF and there is a disagreement between MammoWave output and conventional mammographic imaging, additional examinations may be warranted. These may include US, if not already conducted, particularly for dense breasts, aligning with EUSOBI recommendations due to the reduced sensitivity of conventional mammography in dense breasts.^38^ All output information, including MammoWave’s results and conventional breast examination findings, will be collected and incorporated into this study. At each site, the investigators will prospectively compare MammoWave labels with the reference standard. Furthermore, on the study’s conclusion, the MammoWave labels will undergo centralised review by blinded specialists who will not have access to the reference standard. This review aims to validate the AI-produced data.

Following the study, a retrospective analysis will be conducted to refine an additional AI-generated algorithm using all acquired data. This algorithm will then be employed to re-evaluate the MammoWave data collected during the study, retrospectively reassessing the endpoints.

Regarding blinding strategies, the study will proceed as follows: first, each mammogram (either full-field DM or DBT) will be independently double-read by two radiologists, with consensus or arbitration for any discordant interpretations, in accordance with European breast screening guidelines (European Guidelines on Breast Cancer Screening and Diagnosis, ECIBC). Following this, all the eligible women will be enrolled consecutively, as detailed above. Blinding will be in place for the participants in the study. The output from MammoWave will be automatically transmitted to the responsible Investigator; blinding will be in place for MammoWave analysis.

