#### MammoWave’s AI-powered clinical decision support system

MammoWave’s novel software includes an AI (machine learning-based) classification algorithm. This algorithm has been developed using the clinical data collected in a previous international, multicentric study (ClinicalTrials.gov Identifier: NCT04253366). In particular, the labels (reference standard, ie, the output of conventional breast examination path) collected in such study were used for training and testing, with the aim of optimising the AI-based classification algorithm (to be used, prospectively, within this clinical trial).

This AI-based classification algorithm works on the S_21_ data of each scanned breast, which is a matrix of complex electromagnetic signals derived from the measurement performed for multiple positions of the TX and RX antennas and sampled in frequency. Principal component analysis methods were used to reduce the matrix’s dimensionality and fix the number of components so that at least 95% of the variance in the data is accounted for. Various algorithms were tested (support vector machines (SVM), decision trees, random forests, logistic regression, k-nearest neighbours), using the cross-validation methodology and calculating the performances in terms of specificity and sensitivity.^36^ More specifically, the SVM-based algorithm will be used within this trial to categorise breasts into two groups: WSF (breast With Suspicious Finding), indicating the presence of a suspicious lesion, or NSF (No Suspicious Finding), indicating the absence of a lesion or the presence of a low-suspicion lesion. More details related to algorithm’s validation methodology and performances in terms of specificity and sensitivity can be found in Papini *et al*,^36^ where specificity of up to ~90% and sensitivity of up to ~85% have been reported.

As an example, figure 2 shows MammoWave’s output and reference standard output is also shown.

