Evaluation of the sensitivity of MammoWave in detecting BC according to the American College of Radiology (ACR) BI-RADS classification.^37^Evaluation of the effectiveness of MammoWave versus a conventional reading of digital mammographic images (either 2D or tomosynthesis) and analysis of whether they are equivalent in terms of detection rates of BC (sensitivity),the number of recalls and positive predictive value (for the biopsies performed).Evaluation of the detection rate (sensitivity) of each system according to the type of mammographic radiological finding (microcalcification, mass, asymmetry or architectural distortion group).Evaluation of the impact of breast density (according to the ACR BI-RADS classification^37^ assigned by the radiologist, with or without automatic software if available) on the MammoWave detection rate of BC, number of recalls and positive predictive value (of the biopsies performed).Evaluation of the impact of breast density (according to BI-RADS classification assigned by the radiologist^37^) on the detection rate (sensitivity) of each system depending on the type of finding (microcalcification, mass, asymmetry or architectural distortion group).Comparison of radiological, histological and stage characteristics between the BCs detected by each system.Evaluation of the reproducibility of the AI-based MammoWave software’s results.Evaluation of the improvement in both sensitivity and specificity when retrospectively using AI algorithms to evaluate MammoWave data after its further optimisation with all the data collected in the patients included in the study.Volunteers’ satisfaction related to MammoWave use, through a properly designed questionnaire (given here as online supplemental material), collecting women’s issues during the exam with MammoWave in the language spoken by the women.

Additionally, there is a secondary objective, which is related to MammoWave safety and tolerability assessment. Furthermore, an additional exploratory objective of the clinical study is to establish a predictive model capable of discriminating and classifying lesions in MammoWave outcomes for volunteers with breast lesions, if feasible.

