
#### Study outcomes

The primary outcomes will be measured as follows:

MammoWave’s sensitivity (percentage of ‘true positive’ results) while using an optimised AI-based classification algorithm.MammoWave specificity (percentage of ‘true negative’ results) while using an optimised AI-based classification algorithm.

The secondary outcomes will be measured as follows:

BC detection rates of each system by type of lesion (microcalcification, mass, asymmetry or architectural distortion group).BC detection rates, recall and positive predictive value (biopsy) of each system, also by breast density (types A and B being low-density breasts (fat), C and D high-density breasts (high content of fibroglandular tissue)).BC detection rates of each system by BI-RADS classification.^37^BC detection rates of each system by type of lesion (microcalcification, mass, asymmetry or architectural distortion group) and density (fat or high content of fibroglandular tissue).Programme screening rate, calculated as the proportion of women diagnosed with BC in the study population.BC detection rates of each system by histological type and size of the BC and BI-RADS classification.^37^MammoWave’s AI classification algorithm’s sensitivity (frequency of ‘true positive’ results) and specificity (frequency of ‘true negative’ results) after a retrospective adjustment using the data at the end of the study.BC detection rate, recalls and positive predictive value (biopsy), also by breast density (types A and B or C and D) after retrospective AI adjustment using the data at the end of the study.Programme screening rate, calculated as the proportion of women diagnosed with BC in the study population after a retrospective adjustment using the data at the end of the study.Evaluation of the reproducibility of results comparing the lectures performed at the study centres and the centralised lectures.Volunteers’ satisfaction through a properly designed questionnaire collecting women’s issues during the exam with MammoWave in the language spoken by the women.

Regarding safety outcomes, all the events will be registered, and they will be identified as related or not to MammoWave.

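### The end-of-study algorithm is refined on all trial data and re-scored on the same women, so its reported improvement mixes real learning with optimism

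*Protocol article*

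**What the plan says.** Three places in the protocol article describe the same step.

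- **Study design**, on what follows the study: "a retrospective analysis will be conducted to refine an additional AI-generated algorithm using all acquired data". The next sentence puts that algorithm to work: "This algorithm will then be employed to re-evaluate the MammoWave data collected during the study, retrospectively reassessing the endpoints".
- **Hypothesis and objectives** makes the result a secondary objective: "Evaluation of the improvement in both sensitivity and specificity when retrospectively using AI algorithms to evaluate MammoWave data", with the qualification "after its further optimisation with all the data collected in the patients included in the study".
- **Study outcomes** lists the results as secondary outcomes: sensitivity and specificity "after a retrospective adjustment using the data at the end of the study"; detection rate, recalls and biopsy PPV "after retrospective AI adjustment using the data at the end of the study"; and a programme screening rate, defined as "the proportion of women diagnosed with BC in the study population after a retrospective adjustment using the data at the end of the study".

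The section on the AI-powered decision support system describes the classifier: principal components retaining at least 95% of the variance, then a support vector machine (SVM). It says that candidate algorithms were compared "using the cross-validation methodology and calculating the performances in terms of specificity and sensitivity". That sentence concerns development on the previous study's data. Nothing comparable is attached to the end-of-study refinement.

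**The concern.** A classifier scored on the sample it was fitted to looks better than it will in new women, because part of the fit follows chance features of that sample. The effect grows with the number of fitted quantities per case, and a screening cohort has few cases. Here the article assigns the same women to both fitting and scoring, and calls the result improvement.

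At stake is a secondary result that would appear beside the prospective estimate as if the two were comparable. The prospective labels are produced before the outcome is used. The retrospective labels come from a model that has already seen the outcome. A reader could not tell how much of the difference would persist in new women.

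Two of the adjusted outcomes have a further difficulty. The proportion of women diagnosed depends on diagnosis and not on the label, so recomputing labels cannot move it. Biopsy PPV depends on who was biopsied, and a woman who becomes WSF only under the new algorithm had no work-up triggered by that label.

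**Working it through.** **1. Number of cancers available.** The inputs are in the Number of participants section: target sensitivity 75%, two-sided 95% CI, a stated CI width of 10, prevalence 0.92%, minimum 8000 and maximum 10 000 women.

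Buderer: N = z² × Se(1 − Se) / W² / prevalence. With z = 1.96 and W = 0.10, cancers needed = 1.96² × 0.75 × 0.25 / 0.10² = 72.03, and 72.03 / 0.0092 gives 7830 women (7935 if cancers are rounded up to 73). The stated 8000 is reproduced, provided that 10 points is read as the half-width. At full size the trial expects 10 000 × 0.0092 = 92 cancers.

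**2. Same data or different data?** Fitting set: all acquired data (Study design); all data from included patients (Hypothesis and objectives). Scoring set: the MammoWave data collected during the study (Study design). If all the data are used for fitting, no trial data are held out, and the article does not limit scoring to out-of-fold predictions.

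**3. Size of the optimism.** The documents give no figure, so it was simulated. *Assumptions:* one record per woman, 92 cancers in 10 000 women, k independent standard normal components, a linear discriminant, and the cut-off set at 90% specificity in the fitting data. One component carries a shift d = z(0.90) + z(0.75) = 1.282 + 0.674 = 1.956, so the best attainable sensitivity is 75%. *Compared:* sensitivity on the fitting data and in new women. The simulation was coded and run twice, with 30 replicates (A) and 20 replicates (B).

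| k | A: same data / new women | B: same data / new women | Overstatement (points) |
|---|---|---|---|
| 10 | 76% / 74% | 75.9% / 74.0% | about 2 |
| 20 | 77% / 73% | 75.7% / 73.5% | 2 to 4 |
| 50 | 80% / 71% | 79.2% / 70.8% | 8 to 9 |
| 100 | 83% / 68% | 82.1% / 68.1% | 14 to 15 |

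At k = 5, run B showed no overstatement (73.8% / 74.6%). Simulation error is about 1 point: √(0.75 × 0.25 / 92) = 0.045 per replicate, and 0.045 / √20 = 0.010.

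**4. Weaker signal (run B).** With 60% attainable sensitivity, same data against new women was 62.4% / 57.6% at k = 20, 67.9% / 54.0% at k = 50 and 71.8% / 49.9% at k = 100. With no signal at k = 50 it was 29.3% / 10.1%; run A gave 30% / 10%.

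**5. Does cross-validation remove it?** In run B with 75% attainable, five-fold cross-validation gave 74.1% at k = 10 and 70.4% at k = 50, close to the new-women values. At k = 100 it gave 63.2% against 68.1%, so there it erred on the low side. Each fold fits on only four fifths of the cancers.

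**6. Flexible kernel.** A class-weighted radial-basis SVM was fitted to pure noise (2 replicates; kernel and settings assumed).

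| k | Same-data sensitivity / specificity | Cross-validated sensitivity |
|---|---|---|
| 10 | 100% / 91.2% | 8.2% |
| 20 | 100% / 99.5% | 1.1% |
| 50 | 100% / 100% | 0% |

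A classifier that had learned nothing would pass both targets (above 75% and above 90%) on its own fitting data. This shows what same-data scoring permits. It does not forecast what this trial will find.

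**The case against.** The strongest reply is that same-data scoring is not spelled out as the estimation method. The article condenses a longer protocol and leaves methods to an SAP that is not shown. For the previous study it says in similarly short terms that the labels served for training and testing, and then turns out to mean cross-validation. Out-of-fold scoring over all trial data would also fit the words. This stands in part: the SAP may well add it. It does not remove the point, because the article itself names the data for fitting and for scoring, and its plain reading is that they are the same.

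Other limits stand in full. The size cannot be derived from the documents, and with few components and strong signal it is small.

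Some stronger readings are tempting but unsupported:

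- *The trial's main result is biased by this step.* It is not. The primary outcomes rest on labels generated during the study, and the retrospective versions are listed separately as secondary.
- *Any improvement would be pure artefact, or upward bias is guaranteed.* Real learning from the trial data is possible. Optimism is expected on average but is not certain in a single data set.
- *Adjusted biopsy PPV cannot be obtained.* The objectives define PPV for the biopsies performed, and biopsies also arise through the conventional pathway, so it can be computed. The difficulty is selective verification.
- *The figures are meant to support a later product version.* The documents do not say so.

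**Conclusion.** The concern holds for the secondary retrospective analysis. As written, the refined algorithm's sensitivity, specificity, detection rate and recalls are reassessed on the women used to refine it, so an improvement could not be divided into learning and optimism.

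For a linear rule with 75% attainable sensitivity, the expected overstatement runs from about 2 points at 10 components to 14 to 15 at 100. This rests on 92 cancers, Gaussian components and one record per woman, whereas the trial labels each breast with an SVM of unstated kernel and component count. A flexible kernel could give a much larger gap.

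The adjusted programme screening rate is redundant and biases nothing. Adjusted biopsy PPV is computable but selectively verified. The text should be corrected before the retrospective analysis is run.

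**What to change.** In Hypothesis and objectives, Study design and Study outcomes:

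1. State that the refined algorithm's performance will be estimated only from out-of-sample predictions. Use nested cross-validation grouped by woman (both breasts in one fold), with the principal components, tuning and threshold refitted inside each fold, or evaluate it in new women. Leave-one-centre-out over the nine centres is a useful supporting analysis.
2. Report the paired difference from the labels actually issued during the study, with a 95% CI. The issued labels are the right comparator because the algorithm may be fine-tuned in the first 500 women and updated at the interim evaluation, so there may be no single locked version.
3. Call any same-data figure apparent performance, not improvement.
4. Drop the programme screening rate after retrospective adjustment.
5. Report adjusted biopsy PPV only among biopsies actually performed, with a note that women who become WSF only under the new algorithm had no work-up triggered by that label.

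The cost is computing time, some rewording and probably a smaller reported improvement. Cross-validation may also understate performance somewhat if many components are used. Nothing changes for participants.

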#### Study period

Recruitment started in February 2024; recruitment of the last participant is planned for February 2026. The deadline for the first evaluation of the results is planned for December 2026.

#### Choice of comparator/control intervention

MammoWave’s results (labels provided by its AI-based classification algorithm) will undergo validation against a reference standard, which represents the output of the conventional breast examination pathway. This pathway includes screening mammograms conducted with DM or DBT, integrated with other radiological/histological findings as required by the responsible investigator, following the site’s ongoing procedures and clinical circuit. The reference standard’s results will be categorised as ‘positive’ when BC presence is confirmed by histology (ie, BI-RADS 6), otherwise labelled as ‘negative’ (BI-RADS 1, 2 or 3). Specifically, within this study BI-RADS 4 and BI-RADS 5 are only image suspicion criteria: when a biopsy is performed, they will be categorised as ‘positive’ when BC presence is confirmed by histology (ie, BI-RADS 6), otherwise labelled as ‘negative’ (BI-RADS 1, 2 or 3).

Conventional mammogram studies (2D or tomosynthesis) will adhere to approved protocols and clinical practices for breast screening. Radiological reports and interpretations will align with international guidelines, particularly those set by the ACR.^37^ The radiologists involved in this study will have extensive experience in mammographic interpretation, serving as the benchmark during the study. Details such as single or double screening readings and the utilisation of AI-assisted mammographic reading will be documented at each centre. Additionally, the integration of conventional mammogram studies with other radiological/histological findings will occur when deemed necessary by responsible investigators, who will record relevant variables in the electronic case report form (eCRF) following their usual clinical practice.

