**Methods and analysis:**

10 000 volunteers undergoing regular mammographic breast cancer screening will be recruited across 9 European centres and invited to participate in the clinical study, involving MammoWave testing on both breasts. MammoWave results will be checked against the reference standard, to be intended as the output of conventional breast examination path (with histological confirmation of cancer cases) with 2 years follow-up. Anonymised clinical and MammoWave’s results, including microwave images, associated features and a label provided by the AI-based classification algorithm, will be collected and stored in a dedicated electronic case report form. The prospective study will involve a comparative analysis between the output of the conventional breast examination path (control intervention) and the labels provided by MammoWave’s AI system (experimental intervention). These labels will categorise breasts into two groups: breast With Suspicious Finding, indicating the presence of a suspicious lesion or No Suspicious Finding, indicating the absence of a lesion or the presence of a low-suspicion lesion. This trial aims to provide evidence regarding the novel MammoWave’s AI system for detecting breast cancer in asymptomatic populations during screening.

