#### Study design

This is an open, multicentric, interventional, prospective, non-randomised clinical investigation in which 10 000 volunteers undergoing conventional breast screening examination will also undergo the MammoWave exam. Recruitment of volunteers will be performed at nine centres in different European countries: two Italian hospitals (IRCCS Policlinico San Martino, Genova; and Ospedale San Giovanni Battista—USL Umbria 2, Foligno), one Polish hospital (Pomeranian Medical University Hospital, Szczecin), two Portuguese centres (Champalimaud Foundation, Lisbon and Clínica [name] Ângelo, Lisbon), three Spanish hospitals (Hospital Universitario de Toledo, Toledo; Hospital Universitario Reina Sofía, Córdoba and Hospital General Universitario Morales Meseguer, Murcia) and one Swiss hospital (University Hospital, Zurich). The study (see figure 3) will be composed of two phases:

A preliminary phase is planned to validate and fine-tune the optimised MammoWave’s AI classification algorithm. During this phase, the initial cohort will consist of 500 women recruited from all participating clinical sites. In this preliminary stage, all asymptomatic volunteers will undergo conventional mammography and ultrasound (US) examinations at a minimum to ensure optimal diagnostic accuracy. Suspected cases will follow the standard site-specific pathways, which may include additional tests such as MRI and biopsy.During the second phase, the remaining 9500 women will be enrolled. If the MammoWave’s AI label is positive, an US examination will be conducted (in addition to conventional mammography), particularly for women with dense breasts (recall, as per the European Society of Breast Imaging (EUSOBI), recommendations for screening in dense breasts^38^), unless such examination has already been performed. Suspected cases will follow the standard site-specific pathways, which may include additional tests such as MRI and biopsy. After the enrolment of 3000 volunteers, an interim evaluation will be carried out.

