#### Follow-up

The trial design will allow the comparative evaluation of both the conventional mammogram and MammoWave’s AI solution in terms of cancer detection rate, the number of recalls and positive predictive value, having as reference standard the 2-year follow-up of each volunteer. This follow-up allows to check retrospectively the possible rate of interval BC, and if this was reported as a false positive by MammoWave.

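### The reference rule has no consistent place for an unbiopsied BI-RADS 4/5 breast and leaves out the 2-year follow-up, which can bias sensitivity in either direction

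*Protocol article*

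**What the plan says.** Choice of comparator/control intervention sets the rule for both primary outcomes. The reference is positive "when BC presence is confirmed by histology (ie, BI-RADS 6), otherwise labelled as" negative, and negative is explained as BI-RADS 1, 2 or 3. For the suspicious categories it adds that "BI-RADS 4 and BI-RADS 5 are only image suspicion criteria: when a biopsy is performed, they will be categorised as" positive on histological confirmation, and negative if not. It does not say what happens when no biopsy is performed.

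Biopsy is not mandatory. Study design says: "Suspected cases will follow the standard site-specific pathways, which may include additional tests such as MRI and biopsy". Collected variables likewise records a biopsy only if there was one, and allows an inconclusive result for additional tests.

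Follow-up enters the reference standard in some places and not in others:

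- The abstract describes the conventional pathway "with histological confirmation of cancer cases) with 2 years follow-up".
- The strengths and limitations box says the same in substance.
- The Follow-up section compares the systems "having as reference standard the 2-year follow-up of each volunteer".
- Hypothesis and objectives, and Choice of comparator/control intervention, define the reference with no follow-up condition.

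On timing, Study period says that "recruitment of the last participant is planned for February 2026" and that "The deadline for the first evaluation of the results is planned for December 2026".

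**The concern.** The two sentences of the rule do not fit together. 'Otherwise' makes every breast without histological confirmation negative. The explanation limits negative to BI-RADS 1, 2 or 3, and the BI-RADS 4/5 sentence covers only biopsied cases. Two analysts could code the same unbiopsied BI-RADS 4/5 breast differently, and each could cite the protocol.

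If the literal rule is used, an unverified cancer leaves the sensitivity denominator and joins the non-cancers. Whether sensitivity then rises or falls depends on its MammoWave label. The expected number of cancers is small, so a handful of such cases could move the estimate across the 75% target.

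The missing follow-up condition matters for the same reason. Under Choice of comparator/control intervention alone, a woman whose two years are incomplete counts as cancer-free. Under the Follow-up section she has no final reference status yet.

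**Working it through.** **Inputs from the protocol article.** Target sensitivity 75%, two-tailed 95% CI with width 10, prevalence 0.92%, minimum 8000 and maximum 10 000 participants (all Number of participants); dates (Study period). The number of unbiopsied BI-RADS 4/5 women with cancer is not given, so it is an assumption below.

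**Step 1: reproduce the plan's figure.** Buderer's formula is N = z² × Se × (1 − Se) / d² / prevalence. With d = 0.10 as half-width:

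- cancers needed: 1.96² × 0.75 × 0.25 / 0.10² = 72.03
- participants: 72.03 / 0.0092 = 7830, or 73 / 0.0092 = 7935 after rounding cases up

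Both agree with the stated 8000 to within about 2%. Expected cancers are 8000 × 0.0092 = 73.6 at the minimum and 10 000 × 0.0092 = 92 at the maximum.

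**Step 2: effect on sensitivity.** Let D be the cancers, u the unverified cancers counted as negative, and q the share of those u labelled NSF (missed). Then

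apparent sensitivity = (D × Se − u × (1 − q)) / (D − u).

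With D = 92 and 69 detected (75.0%):

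| u (assumed) | all missed, q = 1 | same miss rate, q = 0.25 | all detected, q = 0 |
|---|---|---|---|
| 2 | 69/90 = 76.7% | 75.0% | 67/90 = 74.4% |
| 3 | 69/89 = 77.5% | 75.0% | 66/89 = 74.2% |
| 5 | 69/87 = 79.3% | 75.0% | 64/87 = 73.6% |

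The estimate can cross the target. With D = 92, true sensitivity 70% (64.4 detected) and u = 8, the range runs from 56.4/84 = 67.1% (all detected) to 64.4/84 = 76.7% (all missed).

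**Step 3: effect on specificity.** Take 10 000 women, 9908 non-cancers and 90% specificity, and add u = 8 to the non-cancers. If all are WSF, specificity is 8917.2/9916 = 89.93%. If all are NSF, it is 8925.2/9916 = 90.01%. The change is below 0.1 point.

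**Step 4: direction.** Study design attaches extra work-up to one label only. A WSF label leads to ultrasound in the second phase, and disagreement with mammography may lead to further examinations. An NSF label triggers nothing. Verification may therefore be more complete for WSF than for NSF cancers, which would push q above the overall miss rate and sensitivity upwards.

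**Step 5: follow-up by the first evaluation.** Recruitment runs from February 2024 to February 2026, 24 months. Two years of follow-up by December 2026 requires recruitment by December 2024. The remaining 14 of 24 months (58% of women, if accrual is even) cannot have it by then.

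**The case against.** There are five serious points on the other side.

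1. The sentence on BI-RADS 4/5 applies only to biopsied cases, so it does not itself label unbiopsied ones negative. This stands. Only the preceding 'otherwise' does so, and its own explanation points the other way. The accurate finding is an inconsistent rule. The plan does not state a deliberate decision to treat these women as cancer-free.
2. If the 2-year follow-up governs, a woman who defers biopsy or has it elsewhere becomes positive once cancer is confirmed. This also stands, and it shrinks the problem in a final analysis with complete follow-up. It does not help women without completed follow-up, because the rule for the primary objective never makes a negative status depend on it. Datasets restricts the full analysis set to women with an evaluable primary result, but does not say whether missing follow-up makes a result non-evaluable.
3. A reader might infer that an NSF label discourages biopsy, because the MammoWave output "will be automatically transmitted to the responsible Investigator". The documents do not support this. Suspected cases follow the site pathway whatever the label, and Study design gives independent double reading of the mammogram as the first step.
4. The ultrasound triggered by a WSF label mainly concerns breasts where MammoWave and mammography disagree, so it bears less directly on a mammographic BI-RADS 4/5. This is fair. It makes an upward bias plausible and does not establish it.
5. Indeterminate results are commonly handled in the SAP, which Statistical considerations promises before the interim analysis. That would be an answer if the protocol were silent. Here it fixes a rule, and the rule conflicts with its other sections.

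**Conclusion.** The concern holds as an inconsistency in the reference standard. An unbiopsied BI-RADS 4/5 breast is negative by one clause and excluded from the negative categories by the explanation attached to it. Follow-up belongs to the reference standard in three places and is absent from the two that define it for the primary objective.

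With about 92 cancers, five unverified cancers counted as negative move 75.0% to somewhere between 73.6% and 79.3%, and specificity hardly changes. This rests on an assumed number of such cancers and on the plan's prevalence. The bias is nil if the omitted cancers share the overall miss rate.

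A reader might conclude that the rule inflates sensitivity. The documents support only that it can bias sensitivity either way, with some reason to expect the upward direction.

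**What to change.** Reconcile Choice of comparator/control intervention and Hypothesis and objectives with the abstract, the strengths and limitations box and the Follow-up section. For the final analysis:

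- **Positive:** cancer confirmed by histology at any time within 2 years.
- **Negative:** BI-RADS 1–3, a benign biopsy, or unbiopsied BI-RADS 4/5, each only with cancer-free 2-year follow-up.
- **Reference indeterminate:** unbiopsied BI-RADS 4/5 without completed follow-up. Leave these out of the main table, add rows that count them all as positive and all as negative, and report their number by MammoWave label.
- **BI-RADS 1–3 without completed follow-up:** state their status explicitly.

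Leaving indeterminate cases out gives the same sensitivity as counting them negative, since neither puts them in the denominator. The all-positive row and the counts by label are therefore what show the possible bias.

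Label the December 2026 evaluation as provisional. Requiring completed follow-up at that date would affect far more than a few women (about 14 of 24 recruitment months).

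The cost is revised wording, extra analysis rows and somewhat wider uncertainty. No extra procedure is needed.
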